**Methods:**

This non-randomized pilot and feasibility study will recruit 20 people with GD. All participants will receive the iCBT intervention through self-learning videos and guided weekly group sessions. The effectiveness of the intervention will be assessed at baseline (week 0), post- treatment completion (week 10), and 6 weeks post-treatment (week 16). The outcomes measured will be the change in gambling symptoms, gambling urges, cognitive distortions, readiness to change, emotional problems, and quality of life of the participants.

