## Methods

### Study design

This study is a pilot and feasibility study with a quasi-experimental design. The protocol adheres to the Standard Protocol Items: Recommendations for Interventional Trials (SPIRIT) checklist (Extended data: Supplementary file 1).
^
15
^ After intake screening, participants will undergo baseline assessment (T1) and will be given treatment for 10 weeks. The treatment will consist of individual online learning sessions delivered through pre-recorded videos, followed by weekly online group therapy sessions with a therapist. Each group therapy session will include five participants. This will be followed by follow up assessment immediately after treatment (T2) and follow up assessment 6 weeks after treatment (T3) (
Figure 1).

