					T1	T2	T3
Gambling symptom severity	G-SAS	Sum of 12 items	Continuous, 8 (mild) to 48 (extreme)	Lower	v	v	v
Gambling urges	GUS	Sum of 6 items	Continuous, 0 to 42, the higher the score indicating the higher the urges/craving	Lower	v	v	v
Gambling- related cognitive distortions	GRCS	5 domains, with the highest percentage being the most dominant domain.	Continuous, 0% to 100% per domain	Lower	v	v	v
Impulsivity	BIS_11	Sum of 30 items	Continuous, 30 to 120, the higher the score indicating the higher levels of impulsivity	Lower	v	v	v
Readiness to change	URICA	Means of each stage of change score	Continuous, means of 9.3 (pre-contemplation), 11 (contemplation) and 12.6 (participation)	Lower	v	v	v
Nonspecific psychological distress	SRQ-20	Sum of 20 items	Continuous, 0 to 20, with scores >5 indicating mental distress	Lower	v	v	v
Quality of life	WHOQOL- BREF	4 domains, with transformed score used	Continuous, 0 to 100 per domain, the higher the score the higher the quality of life	Higher	v	v	v

G-SAS, Gambling Symptom Assessment Scale; PGSI, Problem Gambling Severity Index; GUS, Gambling Urge Scale; GRCS, Gambling Related Cognitions Scale.

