### Development of the iCBT

The iCBT module was developed by researchers from Department of Psychiatry, Faculty of Medicine, Universitas Indonesia and Department of Psychiatry, Flinders Centre for Gambling Research, South Australia. This module consists of 6 parts which will be used as a guide for the therapist in the therapy sessions. The module content for each session is described in
Table 2.

**Table 2. T2:** Description of iCBT module content.

Session	Content	Behavior Change Technique ^ 28 ^	Delivery	Targetted Outcome
1	Building rapport and assessment	-	Online video and online group CBT session	URICA, SRQ-20, WHOQOL-BREF
2	Psychoeducation and objectives	• Goal-setting (behavior) • Goal-setting (outcome) • Discrepancy between current behavior and goal • Pros and cons • Verbal persuasion about capability • Commitment	Online video and online group CBT session	Improvement in GUS, GSAS, GRCS score
3	Understanding gambling disorder Exposure therapy (first exposure task)	• Information about health consequences • Information about social and environmental consequences • Information about emotional consequences • Exposure	Online video and online group CBT session	Improvement in GUS, GSAS, GRCS, and BIS11 score
4	Identification of gambling thoughts and cravings Review of first exposure therapy task and planning of next exposure task	• Problem-solving • Exposure • Graded tasks • Feedback on behavior	Online video and online group CBT session	Improvement in GUS, GSAS, GRCS, and BIS11 score
5-9	Exposure therapy	• Problem-solving • Exposure • Graded tasks • Feedback on behavior	Online video and online group CBT session	Improvement in GUS, GSAS, GRCS, and BIS11 score
10	Relapse and prevention strategies	• Problem-solving • Review outccome goals • Commitment	Online video and online group CBT session	

The contents of iCBT module are largely derived from The Flinders/Statewide Gambling Therapy Service (SGTS) Model of Treatment for Gambling Disorders, a manualized CBT treatment program.
^
29
^
^,^
^
30

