### Data monitoring

Data on adverse events, including hospitalization, arrest, and death, will be collected from the participants’ contact person, treating physician or medical staff. In addition, participants will be interviewed at T2 to determine whether they have experienced any subjective harmful effects (e.g., withdrawal syndrome, increased cravings) after joining this program.

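### Participants are asked about subjective harms only once, at T2 (week 10), so such harms arising in weeks 10–16, or in people not interviewed at T2, may be missed and under-counted.

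*Protocol article*

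**What the plan says.** Data monitoring sets up two routes for harms.

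- **Third parties.** "Data on adverse events, including hospitalization, arrest, and death, will be collected from the" participant's contact person, treating physician or medical staff. No time window is given.
- **Participants.** "participants will be interviewed at T2 to determine whether they have experienced any subjective harmful effects", with examples and a look-back period: "e.g., withdrawal syndrome, increased cravings) after joining this program". This is the only occasion on which participants are said to be asked about harm.

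The abstract places the two later assessments at "treatment completion (week 10), and 6 weeks post-treatment (week 16" respectively. Study design confirms a "follow up assessment 6 weeks after treatment (T3". Table 1 schedules all seven scales at T1, T2 and T3. They include the GUS ("Continuous, 0 to 42, the higher the score indicating the higher the urges/craving") and the SRQ-20 ("Continuous, 0 to 20, with scores >5 indicating mental distress").

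Table 2 introduces exposure in session 3 ("Exposure therapy (first exposure task") and continues it up to session 9; sessions are weekly. Participants and settings says that the study has no drop-out criteria. Delivering the intervention describes a satisfaction form after every session. Providers of iCBT has therapists contact absentees, with attendance as the stated purpose.

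**The concern.** Benefit is followed to week 16, but participants are asked about harm only at week 10. Withdrawal symptoms and increased craving are the protocol's own examples of subjective harm. They are experiences that the participant knows about and others often do not; the Introduction itself notes that gambling problems can stay concealed from outsiders for long periods.

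Three groups of events depend on a question that is not scheduled, or on memory:

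- harms that start after T2;
- harms in people not interviewed at T2;
- early reactions to exposure, which must be recalled at week 10.

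The results are meant to inform the acceptability of the programme and a later conclusive trial. An incomplete count of subjective harms would give that trial a baseline that is too low. The timing of the interview is something the article states, so this is not detail lost in condensing a longer document.

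**Working it through.** The protocol states no harm rate, dropout rate or harm denominator, so there is no figure of its own to reproduce. The check sets out the timing and then illustrates the size under assumptions.

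**Timing, from the document**

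- Weeks after T2 with no stated participant harm question: 16 − 10 = 6, which is 6/16 = 37.5% of the calendar. This is a share of time, not of expected harm.
- Longest recall for an exposure reaction, taking weekly session 3 as week 3: 10 − 3 = about 7 weeks. Later exposure sessions involve less.

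**Illustration**

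From the document: N = 20. Assumed:

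- p1 = 20%, the true risk of any subjective harm by week 10;
- p2, the new risk in weeks 10–16 among those unharmed by week 10;
- d, the share not interviewed at T2;
- r, the risk ratio by week 10 of those not interviewed against those interviewed.

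Formulas:

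- risk among those interviewed: q = p1 / ((1 − d) + d·r);
- recorded share of all 20: (1 − d)·q;
- true share by week 16: p1 + (1 − p1)·p2;
- capture = recorded / true. Recall is taken as perfect.

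Worked case, d = 20%, p2 = 5%, r = 1: q = 0.20 / (0.80 + 0.20) = 0.20. Recorded = 0.80 × 0.20 = 0.16. True = 0.20 + 0.80 × 0.05 = 0.24. Capture = 0.16 / 0.24 = 67%. In people, 3.2 are expected to be recorded out of 4.8 affected.

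Same case with r = 2: q = 0.20 / (0.80 + 0.40) = 0.167. Recorded = 0.80 × 0.167 = 0.133. Capture = 0.133 / 0.24 = 56%.

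| d | p2 | Capture, r = 1 | Capture, r = 2 |
|---|---|---|---|
| 0% | 0% | 100% | 100% |
| 0% | 5% | 83% | 83% |
| 0% | 10% | 71% | 71% |
| 20% | 0% | 80% | 67% |
| 20% | 5% | 67% | 56% |
| 40% | 10% | 43% | 31% |

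**Effect of the denominator**

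If the rate is reported among those interviewed instead of all 20, missed interviews alone (d = 20%, p2 = 0) cause no bias when r = 1: 20% recorded against 20% true. With r = 2 the recorded rate is 16.7% against 20%. Harms after T2 are missed with either denominator.

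**The case against.** The case against a broad reading is strong, and much of it stands.

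- **Other routes exist.** A reader might infer that harms in general go unrecorded after T2 or in people who leave. The text does not support that. Third-party adverse-event collection is not tied to T2 or to completers, and its list of examples is open. Hospitalization, arrest and death are not the gap.
- **Craving and distress are scored at T3.** A rise in either could show in the GUS or SRQ-20. These are scores at one moment, however. They do not ask whether the programme did harm, they can miss a transient rise between visits, and they are also absent for anyone not reached.
- **The interview looks back to joining.** The whole treatment period is covered for everyone interviewed, subject to recall. Weekly sessions also discuss urges, although nothing says this is recorded as harm.
- **Leaving treatment does not by rule end assessment.** With no drop-out criteria, someone who stops could still be interviewed at T2. The text neither promises nor excludes it.
- **Leavers may not be harmed more often.** It is tempting to say that those missing at T2 are the people most likely to have been harmed. That is plausible, but nothing in the document shows it.
- **Some numbers do not bear on under-counting.** The 37.5% of calendar time says little about risk, because weeks 10–16 follow the end of treatment. Upper confidence limits for zero events at a smaller sample size show lost precision, not a lower count.

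What remains is narrow: no participant harm question is stated after T2, or for people not interviewed then, although contacts that could carry one already exist.

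**Conclusion.** The point holds for subjective harms only, and conditionally. Such harms may be under-counted if some participants are not interviewed at T2 or if new ones arise in weeks 10–16. If neither happens, and recall is good, nothing is lost. A reader might conclude that harms will certainly look rarer than they are; the document does not support that, because it gives neither dropout nor harm rates.

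Under the assumed 20% risk by week 10, capture runs from 100% down to 31% across the scenarios tabulated, all of which rest on assumed inputs. The direction, towards too low a count out of all 20, is firmer than the size. Among interviewees only, missed interviews lower the rate only if those missed were harmed more often.

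This is a cheap improvement to harm ascertainment, not a flaw that undermines the study.

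**What to change.** 1. Repeat the T2 subjective-harm questions at the existing T3 assessment. People who missed T2 should be asked about the whole period since joining, and the others about the time since T2.
2. Ask the same questions when therapists contact absent participants, and record the answers.
3. Optionally, add one harm item to the satisfaction form already completed after each session, which would shorten recall.
4. Report the number with any subjective harm out of all 20 enrolled, together with the number actually asked at each time, so that missed interviews are visible.

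In the illustration, if everyone answered at T3 and any absentee contact, capture would return to 100%. The cost is a little participant and therapist time. The article says that recruitment had not begun at submission, so if that is still so the change can apply to every participant.

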### Study status

At the time of submission, the study had not begun any recruitment.

### Dissemination

The results of this study will be disseminated via peer-reviewed journals and international academic conferences. All procedures of this study will be independent from the sponsor. Participant-level dataset will not be made publicly available. Any authors included in the publications will be determined according to authorship guideline of the International Committee of Medical Journal Editors (ICMJE).

## Discussion

The aim of our study is to evaluate the effectiveness, acceptability and feasibility of an online CBT intervention for patients with GD in Indonesia. Previous studies found that only few of those with gambling problems seek professional help.
^
2
^
^,^
^
5
^
^,^
^
23
^ Multidimensional factors including social, cultural, and personal could be contributing to their reluctance to seek treatment. There are a number of obstacles that inhibit help-seeking such as pressure from others to continue gambling, the desire to handle the issues on their own, stigma, secrecy, shame, not admitting problems, practical concerns (such as lack of availability and cost of treatment), worries about treatment, uncertainty, and avoidance.
^
32
^
^–^
^
34
^ Gambling is strictly prohibited under the Indonesian Criminal Code and engaging in such activities is punishable by law.
^
35
^ Although there is currently no research on the subject, it is possible that the illegality of GD is one of the contributing factors to the low rate of help-seeking in GD. Internet-based therapies have the potential to address these barriers by minimizing the stigma associated with seeking treatment, as participants are not required to attend a physical therapy site. Additionally, they help to overcome practical challenges, such as travel time to treatment facilities and scheduling conflicts with other obligations, including childcare and paid work. Furthermore, these therapies can be tailored to meet cultural and language needs to geographically challenging areas, enhancing their acceptability among the target population.
^
36
^ Group CBT model is selected because it is not inferior to individual CBT in terms of efficacy, while being more resource-efficient.
^
37
^
^,^
^
38
^ This approach allows for the treatment of a larger number of individuals with GD, particularly in resource-limited settings, such as those found in LMICs especially Indonesia, where participants are spread across multiple islands. However, maintaining the confidentiality of personal information among participants must be prioritized throughout the therapy sessions.

To our knowledge, our study will be the first to examine the effectiveness, acceptability and feasibility of a CBT program which will be delivered online for patients with GD in Indonesia. The outcome of this study will provide valuable data for the development of iCBT for individuals with addiction, particularly GD in LMIC. This established module may be a beneficial addition to the resources of treatment for GD in practice.

Evidence-based treatments for GD in Indonesia and LMICs in general remain sparse. The proposed study may provide an alternative to conventional CBT when physical accessibility is an issue (as many experienced during the COVID-19 pandemic), or when the patients have limited access to professional help locally. As a result of this study’s findings, iCBT might be applied in a more widespread context and utilized as a module to assist psychiatrists in engaging and treating more GD patients throughout Indonesia.

### Ethical consideration

The study protocol was approved by the Research Ethical Committee of Faculty of Medicine, Universitas Indonesia (approval number: KET-992/UN2.F1/ETIK/PPM.00.02/2023) which was issued on 24
^th^ of July 2023. The study protocol was registered at
ClinicalTrials.gov (NCT number: NCT06171516 on 14
^th^ December 2023). The study will be conducted in accordance with the Declaration of Helsinki 1969, revision 2013.

All participants will be provided with and asked to sign a patient information and consent form (PICF). The results will be submitted for publication after finalizing the study. Personal data will be protected by separating the study data from the participants’ identifiable information and importantly, written agreement will be obtained from participants to never share others’ information with any third party even after the therapy is finished.

## Ethics and dissemination

The study protocol was reviewed and approved by the Research Ethical Committee of Universitas Indonesia on 24
^th^ of July 2023 (approval number: KET-992/UN2.F1/ETIK/PPM.00.02/2023). All participants will be provided with and asked to sign a patient information and consent form (PICF). The study will adhere to the Declaration of Helsinki 1964, revision 2013. The results will be submitted for publication after finalizing the study.

## Trial Registration

The trial is registered on the 14
^th^ of December 2023 at the
ClinicalTrials.gov database with the identifier number NCT06171516.

## Data Availability

No data is associated with this protocol article. OSF: Internet-based cognitive behavioral therapy for individuals with gambling disorder in Indonesia: protocol for a pilot and feasibility study,
https://doi.org/10.17605/OSF.IO/JB7F5.
^
39
^ Licensed under
CC-BY 4.0 International. The project includes:
•Spirit checklist Spirit checklist
